### Adverse reactions

RECAMP-MV: Common mild adverse reactions to MV include injection site reactions (within 24 h), fever (within 7–12 days), or rash (within 7–10 days); all resolve within 1–3 days. Except from febrile seizures, severe adverse reactions are extremely rare (anaphylaxis, thrombocytopenia, and encephalomyelitis) [30]. MV campaigns’ safety profile has been evaluated, and severe adverse reactions seem rare [31–35].

RECAMP-OPV: Common mild adverse reactions to OPV include self-limiting diarrhoea [36]. The only severe adverse reaction is vaccine derived polio, which occurs in 2–4 infants in a birth cohort of one million children receiving 4 doses of OPV during the first months of life [11]. The risk of circulating vaccine derived polio has been markedly lowered with the shift from trivalent (type 1–2-3) to bivalent OPV (type 1 and 3) [37], as 94% of the circulating vaccine derived polio was caused by type 2 [38].

To the extent possible, we are in contact with the adverse events following immunization (AEFI) responsible from each region to register any potential adverse reaction caused by our campaigns.

### Data management

Data collected by the field teams is transported back to Bissau regularly. Data entry assistants enter the data in DBASE, and they also clean the data based on pre-specified cleaning programs. Data collected during the pilot phase will be included in the analyses to obtain sufficient power. Through crosslinks with other data sources, key variables are verified and data entry errors are captured.

### Statistical analyses

Statistical analyses will be performed in STATA by the research group based on data analysis plans which have been reviewed by the data safety and monitoring board (Additional file 1 (RECAMP-MV) and Additional file 2 (RECAMP-OPV)). If further analyses are planned due to new knowledge arising during the trials, potential amendments to the respective data analysis plan will be discussed with the data safety and monitoring board. We will analyse all primary and secondary outcomes based on individual level data as the cluster size varies. We will present confidence intervals of 95%. Absolute numbers of missing values will be presented, when relevant. No missing values will be imputed. No corrections will be made for multiple testing.

#### Primary analysis of the primary outcome

The main conclusion in RECAMP-MV and RECAMP-OPV will be based on a per-protocol analysis. The primary outcome will be analyzed in a Cox proportional hazards model, adjusted by region, pre-trial vaccination coverage, and sex, with age as the underlying timescale. We will use cluster-robust standard errors to account for intra-cluster correlation. Children will enter the analysis on the day of enrolment, and their follow-up will be censored at:
RECAMP-MV: death due to accident, migration or eligibility for a national MV campaign, whichever comes first.RECAMP-OPV: death due to accident, migration, eligibility for any national vaccination campaign, or a maximum of 12 months of follow-up, whichever comes first.

In both trials, hospital admissions due to accidents are ignored but the follow-up time is censored while the child is admitted.

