## Methods/design

### Setting

Guinea-Bissau’s Ministry of Health has implemented national MV campaigns among children aged 9–59 months every third year since 2006 [19], and OPV campaigns more frequently [15]. Despite some fluctuations in reported measles infection cases [20] and MV coverage [21], Guinea-Bissau has a low risk profile of measles (Table 1) and the last recorded case of indigenous wild poliovirus in Guinea-Bissau was in 1999 [22].

**Table 1 Tab1:** Measles infection cases, vaccination coverage and vaccination campaigns in Guinea-Bissau according to WHO’s country data [20, 21]

*Year*	2008	2009*	2010	2011	2012*	2013	2014	2015*	2016	2017
Measles infection cases (number)	12	0	26	0	0	0	1	153	0	11
1st routine measles dose (proportion)	64%	79%	78%	78%	90%	89%	81%	90%	71%	66%

*****Guinea-Bissau’s Ministry of Health implemented a national measles vaccination campaign

*Abbreviation*: WHO=World Health Organization

Bandim Health Project (BHP) follows women of fertile age and children under-five in Guinea-Bissau’s rural population through a health and demographic surveillance system (HDSS). This enables assessment of child mortality and morbidity. In Guinea-Bissau’s nine rural health regions (Oio, Biombo, Gabu, Cacheu, Bafata, Quinara, Tombali, Bubaque, and Bolama), 222 randomly selected geographical clusters with more than 22,000 children under-five are being monitored. The selection process of the geographical clusters has been described elsewhere [23]. Field teams conduct regular visits to all villages in all clusters. At household visits field assistants register pregnancies, and children’s vaccination status, mortality, morbidity, nutritional status, campaigns with other health interventions, migration, and whereabouts if absent [23]. This is the implementation platform of RECAMP-MV and RECAMP-OPV.

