### Design and randomization

The 222 village clusters were randomized to intervention or control clusters stratified by region and access to health services. We defined health service access as vaccination coverage by 12 months of age assessed among children aged 12–23 months [24], using BHP HDSS data from 2015 to 2016. This pre-trial vaccination coverage was based on Bacillus Calmette Guerin (BCG) vaccine, three doses of OPV, three doses of Pentavalent (diphtheria, tetanus, pertussis, hepatitis B, haemophilus influenza type B), and MV. We defined low and high pre-trial vaccination coverage using the median as a cut-off point. Within each of the two coverage strata per region, we assigned one half of the clusters to receive intervention and health check-up, and the other half to receive only health check-up, based on an externally generated random number.

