After consent, the enrolling nurse performs a health check-up of one child at a time (assessing illness, issues with prior vaccination, and measuring axillary temperature, mid-upper-arm-circumference, and weight). If the enrolling nurse experiences that a child is overtly ill, the child’s mother/guardian is given health advice, and if necessary offered health facility transport, irrespective of cluster assignment. Overtly ill children are offered enrolment at a subsequent visit, if recovered.

If a child is assessed healthy in intervention clusters, the child aged 9–59 months is administered a 0.5 ml reconstituted MV from a 10-dose vial by deep subcutaneous injection into the left subscapular region (leftover doses are discarded six hours after reconstitution), and the child aged 0–8 months is administered two oral drops of OPV from a multi-dose vial (leftover doses are discarded after 28 days). If a child is assessed healthy in control clusters, the child is not administered MV or OPV.

All enrolled children are followed through regular household visits by field assistants who collect information on death and hospitalization, among other. The visits are conducted every two months to children < 12 months of age in Oio, Biombo and Cacheu for logistical reasons, and every six months to older children, and in the remaining regions. If a field assistant registers the death of a child, a specially trained field assistant conducts a verbal autopsy at a subsequent visit [28]. An extra follow-up visit is conducted among a subgroup of enrolled children one-two months after enrolment; the mothers/guardians of these children are visited by field assistants to collect information on outpatient visit and maternally reported illness in the elapsed time span. This visit is also utilized to provide a second OPV dose to children aged 0–8 months in intervention clusters. Figure 2 shows the flow from eligibility to follow-up in RECAMP-MV and RECAMP-OPV.

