The major limitation is insufficient blinding. Only blinding health system personnel can make the campaigns appear to have an effect that does not solely depend on the campaigns. However, blinding the research group, field teams and mothers/guardians would require placebo use. Administering another vaccine may trigger NSEs, which could obscure the assessment of the campaigns’ NSEs. Administering saline would be causing many children pain without benefit. However, as death and hospitalization are not subjective, and as their assessment is based on standardized interviews, we expect the risk of differential outcome reporting to be minimized. Though, we do have some speculations about the potential impact of not blinding the mothers/guardians: 1) mothers/guardians in intervention clusters may consider their children as being extra healthy because they have seen their children receive the campaign vaccines. This could make the mothers/guardians less prone to seek help from the health system if their children get ill. Thus, among children whose mothers/guardians state that their children have been ill after enrolment we will assess the proportion of children whose mothers/guardians also state an outpatient visit by cluster assignment. 2) mothers/guardians in intervention clusters could come to know that their children belong to an intervention cluster prior to enrolment because there is no allocation concealment. This could make the mothers/guardians in intervention clusters more motivated to let their children enrol than mothers/guardians in control clusters. Thus, we will assess if there is a difference in the proportion of children whose mothers/guardians choose not to participate for different reasons, by cluster assignment.

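### The per-protocol Cox model does not use the weight, arm circumference and prior vaccination status collected for each child, so it cannot correct measured differences from enrolment after unconcealed cluster allocation

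*Protocol article*

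**What the plan says.** Primary analysis of the primary outcome sets the population and the model for both trials. On the population: "The main conclusion in RECAMP-MV and RECAMP-OPV will be based on a per-protocol analysis". The model is a "Cox proportional hazards model, adjusted by region, pre-trial vaccination coverage, and sex, with age as the underlying timescale", with cluster-robust standard errors and entry on the day of enrolment.

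The coverage term is not the child's own record. Under Design and randomization, "The 222 village clusters were randomized to intervention or control clusters stratified by region and access to health services", with access measured by vaccination coverage, and "We defined low and high pre-trial vaccination coverage using the median as a cut-off point". The child-level terms are therefore sex and, through the timescale, age.

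The trial holds more than this on each child. Under Enrolment and follow-up procedures, the nurse's check-up after consent and before any vaccine consists of "assessing illness, issues with prior vaccination, and measuring axillary temperature, mid-upper-arm-circumference, and weight", and the Abstract offers the check-up in both arms. Under Setting: "At household visits field assistants register pregnancies, and children’s vaccination status, mortality, morbidity, nutritional status".

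The Discussion raises selective enrolment. Guardians in intervention clusters "could come to know that their children belong to an intervention cluster prior to enrolment because there is no allocation concealment", which could make them "more motivated to let their children enrol than mothers/guardians in control clusters". It plans a comparison of non-participation by arm. The article also plans two intention-to-treat analyses and alternative censoring rules as sensitivity analyses, and effect-modifier analyses that include prior MV status in RECAMP-MV.

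**The concern.** Clusters were randomized, but the children in the primary analysis were selected afterwards. Three features leave room for that selection to differ by arm: guardians may learn the allocation before they decide, the field teams know it, and a nurse in the unblinded team judges who is too ill to enrol (Study population, criterion 1).

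If the enrolled children then differ between arms in nutrition or prior vaccination, and these predict death or admission, the per-protocol hazard ratio carries part of that difference. Unlike chance imbalance, a systematic difference is not reflected in the confidence interval. The direction is not known in advance: stronger motivation could bring in healthier children or frailer ones.

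The protocol gives its own reasons to treat these variables as prognostic. Low arm circumference is an exclusion criterion meant to keep out severely ill or immunocompromised children. The premise of both trials is that MV and OPV lower mortality. The Blinding section speculates that a child's vaccination card could influence treatment priority at the health facility.

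**Working it through.** **Step 1. Reproduce the plan's power, to confirm the inputs.** From Sample size considerations and Table 2: 222 clusters, so c = 111 per arm; coefficient of variation k = 0.25; alpha 0.05, taken as two-sided. The Hayes–Moulton formula is

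power = Φ( √{(c−1)(λ0−λ1)² / [(λ0+λ1)/y + k²(λ0²+λ1²)]} − 1.96 ).

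- RECAMP-MV, y = 84, rates 0.017 and 0.0119 (exactly 30% lower): √(0.0028611 / 0.00037096) = 2.777, power 79.3%. The stated 80% reproduces. With the rounded rate of 12/1000 it is 77.6%.
- RECAMP-OPV, y = 40, rates 0.055 and 0.041: √(0.02156 / 0.0026941) = 2.829, power 80.8%. The stated 80% reproduces.

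This formula contains no covariates, so none of the protocol's figures changes with the adjustment set.

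**Step 2. Design-stage standard error of the log hazard ratio, with clustering.** SE = √{[1/(λ0y) + k² + 1/(λ1y) + k²] / 111}.

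- RECAMP-MV (17 vs 12 per 1000): √[(0.7003 + 0.9921 + 0.125)/111] = 0.128. Significance needs an observed hazard ratio of about exp(−1.96 × 0.128) = 0.78.
- RECAMP-OPV (55 vs 41 per 1000): √[(0.4545 + 0.6098 + 0.125)/111] = 0.104. Significance needs about 0.82.

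**Step 3. Spurious hazard ratio from an omitted marker when the vaccine has no effect.** The documents give no imbalance and no prognostic strength, so every value here is an assumption. The marker is taken as independent of the terms already in the model, which makes these upper figures.

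Binary marker with hazard ratio R and prevalence p0 (control) and p1 (intervention): [1 + p1(R−1)] / [1 + p0(R−1)]. Type I error uses the null standard error √{2[1/(λ0y) + k²]/111}, which is 0.117 in RECAMP-MV and 0.097 in RECAMP-OPV.

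| R | p0 vs p1 | Spurious HR | Type I error MV / OPV |
|---|---|---|---|
| 1.5 | 5% vs 4% | 1.02/1.025 = 0.995 | 5.0% / 5.0% |
| 2 | 10% vs 8% | 1.08/1.10 = 0.982 | 5.3% / 5.4% |
| 2 | 10% vs 5% | 1.05/1.10 = 0.955 | 6.8% / 7.7% |
| 3 | 10% vs 5% | 1.10/1.20 = 0.917 | 11.5% / 14.7% |

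Continuous marker with hazard ratio h per SD and a mean difference of d SD: h^d.

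- h = 0.65: d = 0.05 gives 0.979, d = 0.10 gives 0.958, d = 0.15 gives 0.937.
- h = 0.50, d = 0.15 gives 0.901. On the log scale this is 0.104, or 0.104/0.128 = 0.8 SE in RECAMP-MV and 0.104/0.104 = 1.0 SE in RECAMP-OPV.

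**Step 4. Do the planned checks adjust for this?**

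- Non-participation by arm: it can reveal differential enrolment but leaves the hazard ratio unchanged.
- Classic and extended intention-to-treat: these bring non-enrolled children back in, so they estimate the effect in a different population. The per-protocol estimate itself stays unadjusted.
- Effect modifiers: prior MV status in RECAMP-MV, age at first OPV and prior OPV campaign in RECAMP-OPV. They examine variation in the effect. Weight and arm circumference are not among them.

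**Step 5. Would adjusted and primary hazard ratios be comparable?** Control-arm risk is roughly 0.017 × 1.5 = 2.6% in RECAMP-MV and 0.055 × 10/12 = 4.6% in RECAMP-OPV. With events this rare, a gap between the two estimates would mainly reflect imbalance; non-collapsibility of the hazard ratio would add little.

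**The case against.** The strongest reply is that the model is sound as it stands. It contains both stratification factors, sex and age, which is a defensible pre-specified set for a stratified cluster trial. This stands: leaving out individual prognostic covariates is not an error, and chance imbalance belongs to the standard error.

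Second, the Discussion offers differential motivation as speculation, and the field assistant does not disclose the allocation when referring families to the health post. This also stands. A reader might infer that the protocol expects the enrolled groups to differ; it says only that they could.

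Third, the intention-to-treat analyses meet selection more directly, because weight and arm circumference capture guardian motivation poorly. That is fair, and adjustment does not replace them. But they are sensitivity analyses, and the main conclusion rests on the per-protocol estimate.

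Fourth, the two data analysis plans (Additional files 1 and 2) are cited but not at hand and may already hold an adjusted analysis. So it cannot be said that none is planned, only that the model described in the article does not adjust for these variables.

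Fifth, changing a primary model that the monitoring board has reviewed, during data collection and with an unblinded research group, has a cost in credibility. That is a good reason to allow the adjusted model to stand beside the primary one.

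**Conclusion.** The concern holds in limited form. The primary model leaves out three child-level variables that the trial already collects. Post-randomization, unconcealed enrolment combined with a per-protocol primary analysis gives a specific reason to use them. Under the assumed values the hazard ratio moves by about 0.5–2% for a modest imbalance, about 4–6% in intermediate cases, and about 8–10% only for a large imbalance in a strong risk marker. The last is at most about one design-stage standard error.

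A reader might infer that any imbalance passes in full into the hazard ratio. The documents do not support that: age, sex, region and coverage stratum absorb part of it, the exclusion criteria trim the highest-risk children in both arms, and the effect of the rest depends on quantities the protocol does not give. Nor would adjustment settle the selection question, since differences in unmeasured health would remain.

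**What to change.** Add to the Cox model: enrolment weight given age and sex; arm circumference where measured; and prior vaccination status as recorded up to enrolment (MV status in RECAMP-MV, number of OPV doses given age at enrolment in RECAMP-OPV, because dose count depends heavily on age). If the reviewed primary model is kept because data collection is under way, pre-specify this adjusted model and report it beside the primary result. If the unshown analysis plans already contain it, a cross-reference is enough.

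Show the same variables by arm among enrolled children. Keep children with missing measurements through a missing category, so that the no-imputation rule does not remove them from the adjusted model.

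The cost is a few lines of plan text, a few model terms, the handling of missing measurements and a documented amendment discussed with the monitoring board. No new data are needed.

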#### Secondary outcomes

In per-protocol analyses, we will assess the secondary outcomes: non-accidental mortality, non-accidental repeated morbidity, and cause-specific primary outcome. These secondary outcomes will be analyzed in Cox proportional hazards models as described for the primary outcome. Furthermore, we will analyse outpatient visits and maternally reported illnesses occurring 1–2 months after enrolment in per-protocol analyses using log-binomial regression models adjusted for region, pre-trial vaccination coverage, and sex. In RECAMP-OPV, we will furthermore analyze weight and MUAC 1–2 months after enrolment using multiple regression models adjusted for region, pre-trial vaccination coverage, and sex.

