### Intervention

RECAMP-MV: We offer one dose of a WHO pre-qualified monovalent live attenuated measles vaccine (Edmonston-Zagreb strain from Serum Institute of India) to children aged 9–59 months in intervention clusters.

RECAMP-OPV: We offer one dose of a WHO prequalified standard bivalent OPV to children aged 0–8 months in intervention clusters. To mimic the way most OPV campaigns are implemented, we initiated the RECAMP-OPV trial with two visits one month apart where logistically feasible. At the second visit, a second dose of OPV is offered to children in intervention clusters, while children in both control and intervention clusters are health examined and weighed.

The cold chain for both vaccines is documented. We provide the MV and OPV campaign vaccinations independently from Guinea-Bissau’s routine child vaccination program [26] (Fig. 1).

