### Outcomes

The primary outcome for each trial is defined as a composite outcome to ensure sufficient power. It consists of:
non-accidental mortality ornon-accidental morbidity (first non-fatal hospitalization with overnight stay)

The secondary outcomes assess other health measures. They consist of:
non-accidental mortalitynon-accidental repeated morbidity (at least one non-fatal hospitalization with overnight stay)cause-specific primary outcome (malaria, diarrhea, and respiratory infections [29])proportion of non-accidental outpatient visits and non-accidental maternally reported illnesses in a sub-group 1–2 months after enrolment in the elapsed time spanFurthermore in RECAMP-OPV: weight at the extra follow-up visit 1–2 months after enrolment

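### Outpatient visits and reported illness are counted over one to two months since enrolment, but the stated model for them contains no term for elapsed time

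*Protocol article*

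**What the plan says.** Four statements in the protocol article bear on this point.

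- **Timing of the visit** (Enrolment and follow-up procedures): "An extra follow-up visit is conducted among a subgroup of enrolled children one-two months after enrolment".
- **What is asked** (same section): guardians are visited "to collect information on outpatient visit and maternally reported illness in the elapsed time span". The Outcomes section agrees, listing the "proportion of non-accidental outpatient visits and non-accidental maternally reported illnesses in a sub-group 1–2 months after enrolment in the elapsed time" span. The recall period is therefore the time since enrolment, not a set number of days.
- **The model** (Statistical analyses, Secondary outcomes): the two outcomes are analysed "using log-binomial regression models adjusted for region, pre-trial vaccination coverage, and sex". Mortality, repeated morbidity and the cause-specific outcome are treated differently in the same paragraph: "These secondary outcomes will be analyzed in Cox proportional hazards models as described for the primary outcome".
- **What else happens at the visit**: in RECAMP-OPV, "This visit is also utilized to provide a second OPV dose to children aged 0–8 months in intervention clusters". The Intervention section says "we initiated the RECAMP-OPV trial with two visits one month apart where logistically feasible", and adds that children in both arms are examined and weighed at the second visit.

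**The concern.** A child asked at 60 days has had twice as long to fall ill or attend a clinic as a child asked at 30 days. A log-binomial model of any event since enrolment treats the two answers as equivalent. Region, vaccination coverage and sex do not measure exposure time, although region may absorb some of its variation.

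Two consequences follow. First, even if the spans are distributed alike in both arms, they add variation unrelated to the vaccine. Second, if the mean span differs between arms, the model attributes the resulting difference in proportions to the campaign.

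The second consequence deserves attention here because the field teams making the visits are not blinded (Discussion: "However, blinding the research group, field teams and mothers/guardians would require placebo use", and no placebo is used). In RECAMP-OPV, in addition, only intervention clusters receive a dose at the visit. These facts make a difference in timing possible. They do not show that one exists.

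**Working it through.** The article states no event risk, effect size or power for these outcomes, so there is no figure to reproduce. The calculation below illustrates the case of no true vaccine effect.

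**Inputs**
- Span: 30 to 60 days, from the one-to-two-month visit.
- Risk of an event within 30 days, p30: not in the article. Assumed 30%, with 10%, 20% and 50% to show the range.
- Event rate: assumed constant over the span.
- Mean spans by arm: assumed. Each arm is evaluated at its mean span.

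**Formulas**
- Daily rate λ = −ln(1 − p30)/30
- Risk by day d = 1 − exp(−λd)
- Apparent risk ratio = risk at the intervention span ÷ risk at the control span

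**Effect of the span itself.** With p30 = 30%, λ = 0.3567/30 = 0.01189 per day. The 60-day risk is 1 − 0.70² = 51%, or 1.7 times the 30-day risk. The multiple is 1.9 at p30 = 10% (19% v 10%) and 1.5 at p30 = 50% (75% v 50%).

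**Apparent risk ratio with no true effect, p30 = 30%**

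| Mean span, intervention v control (days) | Proportions | Risk ratio |
|---|---|---|
| 45 v 45 | 41.4% v 41.4% | 1.00 |
| 42 v 45 | 39.3% v 41.4% | 0.95 |
| 40 v 45 | 37.8% v 41.4% | 0.91 |
| 40 v 50 | 37.8% v 44.8% | 0.84 |

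For 40 v 45 days the ratio is 0.90 at p30 = 10%, 0.90 at 20% and 0.93 at 50%, so the result depends little on the assumed risk.

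**How large a gap could arise by chance?** Suppose cluster mean spans are uniform over 30–60 days, so SD = 30/√12 = 8.7 days. With 111 clusters per arm (222/2), the standard error of the difference in mean span is 8.7 × √(2/111) = 1.2 days. The size of the subgroup is not given; with 30 clusters per arm it would be 8.7 × √(2/30) = 2.2 days. At p30 = 30%, one day (44 v 45) gives 40.7% v 41.4%, a ratio of 0.98.

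**Noise when timing is equal.** Under the same uniform spread and p30 = 30%, write E for the average over days 30 to 60:
- E[exp(−λd)] = (0.70 − 0.49)/0.3567 = 0.5888, so mean risk = 0.411
- E[exp(−2λd)] = (0.49 − 0.2401)/0.7133 = 0.3503
- SD of risk = √(0.3503 − 0.5888²) = 0.061
- Coefficient of variation = 0.061/0.411 = 0.15

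If spans vary by cluster, timing alone would thus create a between-cluster coefficient of variation of about 0.15.

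**With elapsed time modelled.** Under a constant rate, ln(−ln(1 − risk)) = ln λ + ln d. A complementary log-log model with ln d as offset therefore recovers a ratio of 1.00 in every row of the table.

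**The case against.** The strongest reply is that no bias has been shown. The Intervention section plans the second visit one month later for the trial as a whole and has children in both arms examined at it. The follow-up section describes one extra visit with no arm-specific schedule. RECAMP-MV has no second dose. No passage says that field teams choose visit dates. All of this stands. A reader might infer from the second dose that intervention clusters are visited earlier or more punctually, but the article does not support that.

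Chance is also unlikely to do much. Under the uniform assumption with 111 clusters per arm, a 5-day gap is more than four standard errors (5/1.16 = 4.3). With 30 clusters per arm it is 2.2. A gap of that size would usually need a systematic cause, and none is documented.

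A reader might also infer that a few days' difference could imitate the effect the trials are looking for. That does not hold either. The 30% and 25% reductions are targets for the primary composite, and no target is stated for these two outcomes. At p30 = 30% and a control mean of 45 days, a false ratio of 0.75 would need an intervention mean of about 31 days, a 14-day gap.

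Finally, the data analysis plans are additional files that are not shown here, and they may deal with elapsed time. That tempers the point but does not remove it. The article does not leave the method open: it names the model and its adjustment variables, and elapsed time is not among them.

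**Conclusion.** The point holds in a limited, conditional form. As stated, the analysis counts events over a span that can differ two-fold between children and does not account for that span. With equal timing in the two arms the cost is imprecision, not bias under the null. With unequal timing, the false effect at an assumed 30% 30-day risk is about 5% for a 3-day gap in means and 9% for a 5-day gap. These sizes rest on a constant event rate and on risks and spans that the article does not give.

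The article does not show that timing differs by arm. The issue is confined to two secondary outcomes measured in a subgroup. The primary outcome uses Cox regression, which accounts for follow-up time, and is unaffected. The change is still worth making because it is cheap and removes a possible explanation for any difference found.

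**What to change.** For outpatient visits and maternally reported illness, include the enrolment-to-visit interval in the model. One option is binomial regression with a complementary log-log link and log(days elapsed) as offset, keeping the stated adjustment variables. The other is to add the interval as a covariate to the log-binomial model, which keeps the risk ratio. Tabulate the interval by arm in each trial, so that readers can see whether timing was balanced.

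The cost is a short change to the analysis plan and one table. Enrolment dates are needed already, because children enter the Cox analysis on that day. The article does not state that the date of the extra visit is recorded; this is assumed and should be confirmed. The offset model reports a rate ratio instead of a risk ratio and assumes a roughly constant event rate over the span. Restricting the count to a fixed window would also equalise exposure, but it needs event dates that the article does not say are collected, so modelling the interval is the safer choice.

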### Study population

Children living in BHP’s rural HDSS are eligible to enter RECAMP-MV if 9–59 months of age and RECAMP-OPV if 0–8 months of age. A child is excluded if it: 1) is considered overtly ill by the enrolling nurse or 2) has an axillary temperature > 39 °C or 3) is aged > 6 months and has a mid-upper-arm-circumference < 110 mm or 4) has experienced an allergic reaction after a prior vaccination or 5) is followed in another ongoing BHP trial in rural Guinea-Bissau (i.e. children from RECAMP-OPV will not be enrolled into RECAMP-MV once they turn 9 months old, and children who are < 2 months old and enrolled in a randomized trial giving BCG and OPV at a home visit shortly after birth [25] will not be enrolled into RECAMP-OPV). Criteria 1–4 ensure that we avoid enrolment of severely acutely ill or immunocompromised children, and these criteria are based on WHO recommendations [10, 11], which we have translated into local practice. Criteria 5 is set to avoid data interpretative issues.

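### The log-binomial models for outpatient visits and reported illness omit age, which every Cox model controls; adding age at enrolment is a cheap safeguard with a probably small effect

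*Protocol article*

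**What the plan says.** Under Primary analysis of the primary outcome, the Cox model is "adjusted by region, pre-trial vaccination coverage, and sex, with age as the underlying timescale". Under Secondary outcomes, this carries over to non-accidental mortality, repeated morbidity and the cause-specific outcome: "These secondary outcomes will be analyzed in Cox proportional hazards models as described for the primary outcome". In all of these models children are compared at the same age.

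For the two binary outcomes the same section says "we will analyse outpatient visits and maternally reported illnesses occurring 1–2 months after enrolment in per-protocol analyses", and gives the model as "using log-binomial regression models adjusted for region, pre-trial vaccination coverage, and sex". Age is not in that list. The regression models for weight and MUAC in RECAMP-OPV have the same three covariates, again without age.

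Three design features bear on this:
- **Age range** (Study population): children are "eligible to enter RECAMP-MV if 9–59 months of age and RECAMP-OPV if 0–8 months of age".
- **Subgroup** (Enrolment and follow-up procedures): "An extra follow-up visit is conducted among a subgroup of enrolled children one-two months after enrolment". Its size is not given.
- **Concealment** (Discussion): guardians could learn the cluster's assignment "prior to enrolment because there is no allocation concealment", and the article accepts that this could alter willingness to enrol.

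**The concern.** The covariate list appears to have been carried from the Cox models to the log-binomial models without the age control that the timescale supplied. Age at enrolment is a baseline value known for every child, because it decides which trial the child enters. Leaving it out while keeping sex is hard to justify.

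What is at stake is limited. Clusters were randomised, but children are recruited afterwards, by staff and guardians who may know the assignment. If the ages of those who come forward differ between arms, and illness or visits depend on age, the difference passes into the risk ratio. These outcomes also have less protection than the primary one: the article lists intention-to-treat sensitivity analyses for the primary outcome only.

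**Working it through.** **The plan's own figures.** The article gives no risk, age gradient, subgroup size or power for these two outcomes. Its 80% power refers to the composite primary outcome. That figure reproduces with the Hayes–Moulton formula, power = Φ(√[(c−1)(λ0−λ1)² / {(λ0+λ1)/y + k²(λ0²+λ1²)}] − 1.96), with c = 111 clusters per arm and k = 0.25:
- RECAMP-MV (17 v 11.9 per 1000, y = 84): √7.71 − 1.96 = 0.82, so 79.3%. With the rounded 12 per 1000 it is 77.6%.
- RECAMP-OPV (55 v 41.25 per 1000, y = 40): √7.70 − 1.96 = 0.81, so 79.2%.

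Nothing below affects those figures.

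**Assumptions for RECAMP-MV.** Ages are uniform over 9–59 completed months, so the bands 9–23, 24–35 and 36–59 have weights 15/51, 12/51 and 24/51 and midpoints 16.5, 30 and 48 months. Three sets of illness risk by band are tried.

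**Precision, ignoring clustering.** Share of variance explained by age = Var(p)/[p̄(1−p̄)]. The standard error without age is then about 1/√(1−share) times the standard error with age.

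| Risks by band | p̄ | Var(p) | Share | SE ratio |
|---|---|---|---|---|
| 35/25/15% | 0.232 | 0.00734 | 4.1% | 1.02 |
| 50/35/25% | 0.347 | 0.01132 | 5.0% | 1.03 |
| 45/30/15% | 0.274 | 0.01651 | 8.3% | 1.04 |

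**Effect of a 2-month age difference.** Slope per month = ln(oldest risk/youngest risk)/(48 − 16.5), and the apparent risk ratio with no vaccine effect = exp(2 × slope):
- 50/35/25%: slope −0.0220, risk ratio 0.957.
- 35/25/15%: slope −0.0269, risk ratio 0.948.
- 45/30/15%: slope −0.0349, risk ratio 0.933.

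**Simulation with clustering.** There were 222 clusters of 20 children (assumed), k = 0.25, no true effect and 150 runs per scenario. A log-link Poisson model with cluster-robust standard errors stood in for the log-binomial, without the other covariates. Mean risk was 10% or 30%, and the youngest-to-oldest risk ratio was 2 or 3.
- *Arms balanced on age:* the standard error without age was 1.002–1.017 times that with age. Mean estimates were near zero either way.
- *Arms shifted by 4% of the age range* (2.04 months in RECAMP-MV, 0.36 month in RECAMP-OPV): mean log risk ratio without age was −0.024 to −0.049, that is, a risk ratio of about 0.95–0.98. Adding age removed most of this. Coverage of the 95% interval was 0.88–0.95 without age and 0.94–0.97 with it. With 150 runs, the simulation error of a coverage near 0.95 is √(0.95 × 0.05/150) = 0.018, so these coverages are rough.

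**How unusual is 2 months?** Uniform ages have SD 51/√12 = 14.7 months. With 222 × 20 = 4,440 children (2,220 per arm) and no clustering of age, the standard error of the difference in mean age is 14.7 × √(2/2,220) = 0.44 month. With 1,000 children it is 14.7 × √(2/500) = 0.93 month. Two months is therefore over 4 or about 2 standard errors. A chance difference of 0.5 month would move the risk ratio by 0.5 × 0.0136 = 0.7% to 0.5 × 0.0349 = 1.7%, where 0.0136 = ln 2/51 is the flattest slope tried.

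**The case against.** A short prespecified covariate list is valid in a randomised comparison, and a binary outcome over a fixed window needs no timescale. "The 222 village clusters were randomized to intervention or control clusters stratified by region and access to health services", so chance differences in age cause no systematic bias and are already reflected in the confidence interval. This stands.

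Three stronger readings are tempting, and the documents do not support them:
- *That age confounds these two results.* This would need enrolment that differs by age between arms. The Discussion concedes missing concealment and possibly different motivation, but nothing there links either to the child's age. Two months is well outside chance for a large subgroup, so that scenario describes selective enrolment rather than chance.
- *That the outcomes lose material precision.* The calculations show a loss of a few per cent of the standard error at most.
- *That the planning rates of 70 and 20 per 1000 person-years prove a strong age gradient in these outcomes.* Those rates compare the two trials on death or hospitalisation. They say nothing direct about mild illness or outpatient visits by age within either trial.

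The data analysis plans (Additional files 1 and 2) are not shown and may include age. If they do, the article's covariate list should be brought into line. The omission itself is stated in the article and does not rest on what those files contain.

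**Conclusion.** The point holds as an inconsistency and a missing safeguard. Age is controlled in every Cox model and in neither log-binomial model. The precision loss is about 0–2% of the standard error under most assumed gradients and about 4% under the steepest. With age-balanced enrolment there is no systematic bias. If selective enrolment produced a 2-month difference in mean age in RECAMP-MV, the risk ratio would move by roughly 2–7%, to about 0.93–0.98 when the truth is 1. In RECAMP-OPV, a 0.36-month shift moved it to about 0.95–0.97 in the simulation.

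The illness risks, age gradients, subgroup size and age shifts are all assumptions, since the article gives none of them. The primary outcome and its conclusion are not affected.

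**What to change.** Under Secondary outcomes and in both data analysis plans, add age at enrolment to the covariates of the log-binomial models in both trials. Use a few broad age bands or a linear term, because many narrow bands or a spline on top of nine regions would make non-convergence more likely. Name the fallback in advance: a log-link Poisson model with cluster-robust standard errors, which estimates the same risk ratio.

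The weight and MUAC models in RECAMP-OPV could take the same term. Age may well matter more for those measures in infants, but the article gives no figures to size it.

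The cost is one extra covariate and a slightly higher risk of non-convergence, which the fallback handles. No new data are needed.
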